### Plans to promote participant retention and complete follow-up

In order to enhance participant retention, follow-up visits are coordinated to reduce burden and optimize adherence. The scheduled MRIs are performed in conjunction with study visits, accordingly, we can avoid additional appointments for the sole purpose of MRI. MRI is performed on a scanner next to the outpatient department. Participants receive direct DECT telephone contact numbers and email addresses of the study team members.

A complete and condensed overview of the study visits and procedures is given in Table 2.

**Table 2 Tab2:** Study assessments alongside the visits 1-4

Schedule of assessments				
Visits	1	2	3	4
	Screening and baseline	Follow-up	Follow-up	End-of-study
Months after enrollment	0	3	6	12
Assessment				
Informed Consent	x			
Medical History	x	x	x	x
NIHSS	x	x	x	x
mRS	x	x	x	x
MRI	x		x	x
Basic NPA	x	x	x	x
Extended NPA	x			x
NVDU	x	x	x	x
Biomarkers	x	x	x	x
Blood Laboratory	x	x	x	x

NIHSS, National Institutes of Health Stroke Scale, mRS, modified Rankin Scale; MRI, Magnetic Resonance Imaging; EQ-5D, EuroQol 5 Dimension; extended NPA, Neuropsychologic Assessment; NVDU, neurovascular Doppler ultrasound; biomarkers: refers to blood-based biomarkers

### Benefit–risk assessment

Participation in the study is associated with low additional risks. The potential risks are minimal and mainly related to blood sampling and MRI examinations [2]. The MRI examinations are conducted without contrast agents, and all participants are comprehensively informed about potential discomforts and contraindications during the consent process.

There is no direct therapeutic benefit for participants. However, participants and/or their treating physicians may receive additional diagnostic information regarding disease progression and corresponding clinical counseling.

Given the minimal procedural risks and the substantial scientific value of identifying blood-based biomarkers for CSVD activity and progression, the overall benefit–risk ratio of the study is considered favorable.

### Data collection and management

Data will be collected and managed using REDCap (Research Electronic Data Capture), a secure, web-based electronic data capture platform. REDCap provides role-based access control, audit trails, automated data validation rules, and secure data storage. Study data will be entered directly into electronic case report forms (eCRFs) by authorized study personnel. Regular data quality checks and plausibility controls will be performed throughout the study to ensure data completeness, accuracy, and traceability in accordance with Good Clinical Practice (GCP) principles.

### Data management and confidentiality

Participants data will be pseudonymized and stored at a local in-house password-protected server. The server protection strategy is provided according to critical infrastructures (KRITIS) standards (https://www.bsi.bund.de/DE/Themen/Regulierte-Wirtschaft/Kritische-Infrastrukturen/Allgemeine-Infos-zu-KRITIS/allgemeine-infos-zu-kritis_node.html). Access to personal study participant data is provided to members of the study team in exclusion. Radiologic assessment is performed after data pseudonymization. In case that a participant withdraws from study participation, he/she will have the option to have all study-related data deleted. All study documents are stored securely for up to ten years after the closure of the registry. Data protection follows the German Federal Data Protection Act. A contact to the federal data protection authority is provided to all participants (www.baden-wuerttemberg.datenschutz.de/kontakt-aufnehmen/*).* Participants can review their data, request copies or corrections and communicate complaints or concerns with authorities.

### Statistical methods

#### Methods of analyses

The statistical analysis will be purely descriptive. Categorical variables will be summarized using absolute and relative frequencies, while continuous variables will be described using the mean and standard deviation or the median, interquartile range, and minimum and maximum values, as appropriate. Group differences will be assessed according to the measurement scale and distribution using the t-test or Wilcoxon signed rank test for continuous variables, and the chi-square test or Fisher’s exact test for categorical variables. To investigate temporal changes in parameters, individual slopes will first be estimated using linear mixed-effects models with random intercepts for participants to account for within-subject correlation. They will be subsequently compared between groups. In a further step, notable group differences will be explored using appropriate regression methods (linear regression, logistic regression, and, if applicable, mixed-effects models).

Differences in follow-up imaging with regard to the number and volume of radiological markers of CSVD will be analyzed using the Wilcoxon rank-sum test. Associations between continuous variables will be examined using scatter plots; where appropriate, Pearson or Spearman correlation coefficients will be calculated. Longitudinal data (e.g. the course of one or more biomarkers) will be illustrated by scatter/dotted plots and spaghetti plots, as appropriate. All statistical tests will be conducted using a two-sided significance level of α = 0.05. No adjustment for multiple testing will be performed. Given the exploratory nature of the study, all statistical test results will be interpreted as hypothesis-generating rather than confirmatory. Statistical analyses will be performed with R, The R Project for Statistical Computing with the latest version available (currently 4.5.3).

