**Methods:**

In this single-center, prospective observational cohort study at the University Hospital Ulm, Germany, up to 180 adults with MRI-proven evidence of CSVD will be recruited and stratified into three groups: (1) CSVD without acute ischemic stroke, (2) CSVD with acute lacunar ischemic stroke, and (3) CSVD with territorial ischemic stroke. Participants will undergo comprehensive assessments at baseline, at 3, 6, and 12 months after enrollment. The primary outcome is defined as longitudinal changes of White Matter Hyperintensities (WMH) volumes. Secondary outcomes upon one year include DTI-derived measures, changes in blood biomarkers, cognitive performance, clinical functional measures, and incidence of new cerebrovascular events. Imaging, neurovascular ultrasound, and neuropsychological assessments will be conducted using standardized protocols. Clinical primary and secondary outcomes will be correlated to post-mortem CSVD pathology in the brain in prospectively studied patients, who have consented to autopsy.

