### Secondary outcomes

Secondary outcomes include changes of DTI-derived measures, blood biomarker quantifications, in neuropsychological test results over time, novel cerebral ischemic events, myocardial infarction, the clinical disease course as marked by the modified Rankin Scale score (mRS) and quality of life upon 12 months.

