#### Sample size

We aim to include 60 patients in the three study groups, resulting in a maximum total number of 180 patients. We expect a drop-out proportion of 25%, relating to difficulties of mobility and morbidity for adherence in follow-up visits of patients with territorial brain ischemia in particular and considering the rural area surrounding the region of Ulm, Baden-Württemberg, Germany. The calculation of sample size is not based on a confirmatory study aim, but is exploratory and mirrors our experiences made in the pilot study of the recruitment that can be expected and delivered in our clinical setting in Ulm.

As an illustration of sensitivity: in a pilot subset (unpublished data) with paired manual WMH volumetry (17 patients), the mean 12-month WMH volume change was 5.30 mL (SD 6.03; standardized within-subject effect d_z ≈ 0.88). A within-group comparison detects a change of this magnitude at ~ 80% power (two-sided α = 0.05) in ~ 10 patients per group. With 60 patients per group (≈ 45 completing follow-up after the anticipated 25% drop-out), the planned cohort is sensitive to within-subject WMH changes as small as d_z ≈ 0.36 (at 60 per group) to 0.42 (at 45 per group), i.e. ≈ 2.2–2.5 mL, well below the 5.30 mL observed in the pilot data, and, for exploratory between-group comparisons, to standardized differences of d ≈ 0.51 (at 60 per group) to 0.59 (at 45 per group), a ≈ 3.1–3.6 mL difference in WMH change between groups.

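### The methods stated for new cerebrovascular events and myocardial infarction take no account of follow-up time, although 25% drop-out is expected

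*Protocol article*

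**What the plan says.** The abstract (Methods) lists "incidence of new cerebrovascular events" among the one-year secondary outcomes. The Secondary outcomes section of the main text lists "novel cerebral ischemic events, myocardial infarction", assessed over 12 months.

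Under Methods of analyses, the general rule is "Categorical variables will be summarized using absolute and relative frequencies". Groups are to be compared with "the chi-square test or Fisher’s exact test for categorical variables", and logistic regression is named for further exploration. The mixed-effects models are introduced for parameter slopes and the rank-sum test for imaging markers. No method based on person-time or censoring is named. The section does not mention the event outcomes by name, fixes no denominator for them, and does not say how patients lost before month 12 are counted.

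On follow-up, the Sample size section says: "We expect a drop-out proportion of 25%, relating to difficulties of mobility and morbidity for adherence in follow-up visits of patients with territorial brain ischemia". It adds that this applies to those patients in particular, and gives the rural catchment as a further reason. No group-specific rate is stated, and the calculation applies 25% to every group (about 45 completers out of 60).

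**The concern.** An incidence over 12 months depends on how long each patient was watched. A plain proportion treats everyone in its denominator as fully observed. The article expects a quarter of patients not to be, and expects the problem particularly in one of the three groups being compared.

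The choice of denominator then matters:

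- **All enrolled:** a patient last seen at month 3 without an event counts as event-free for the whole year, so incidence is too low. If drop-out differs by group, the comparison between groups is distorted as well.
- **Completers only:** events recorded before a patient left are thrown away. The proportion is also biased if drop-out is related to events, which is possible because morbidity is one of the stated reasons for drop-out.

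At stake are the reported 12-month incidences, the group contrast in events, and any logistic model relating biomarkers to events.

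**Working it through.** **Inputs from the article:** 60 patients per group, 25% drop-out, 12 months of follow-up.

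**Inputs assumed, because the article gives none:** true 12-month risk p = 10% in every group; timing of drop-out; drop-out by group.

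**The plan's own figure:** 60 × (1 − 0.25) = 45 completers per group, as stated. There is no event rate or event-based power to reproduce.

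**Step 1, enrolled denominator, equal drop-out.** Take a constant event hazard l = −ln(1 − p) and an independent constant drop-out hazard m = −ln(1 − D). The expected observed proportion is l/(l + m) × [1 − (1 − p)(1 − D)].

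- p = 0.10 gives l = 0.1054; D = 0.25 gives m = 0.2877.
- 0.1054/0.3930 × (1 − 0.90 × 0.75) = 0.268 × 0.325 = 0.087.
- The reading is 8.7% instead of 10%, about 13% too low in relative terms. True risks of 5% and 20% also give about 13%.
- Simpler check: with drop-out even over the year, observed time is 1 − 0.25 × 0.5 = 87.5% of the full time.
- Extreme: if all drop-outs leave right after baseline, the reading is 0.75 × 10% = 7.5%.
- With 25% in every group, the ratio between groups stays at 1.

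**Step 2, enrolled denominator, unequal drop-out (assumed splits).** The true ratio is 1. The first two rows apply the Step 1 formula with an overall mean of 25%; the last two use the share of time observed.

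| Drop-out, other group vs territorial | Timing | Apparent values | Ratio, territorial to other |
|---|---|---|---|
| 17.5% vs 40% | constant hazard | 9.1% vs 7.9% | 0.86 |
| 12.5% vs 50% | constant hazard | 9.4% vs 7.3% | 0.77 |
| 15% vs 35% | even over the year | 92.5% vs 82.5% of time | 0.89 |
| 15% vs 35% | last seen at month 3 | 88.75% vs 73.75% of time | 0.83 |

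If all drop-outs left right after baseline, the first two splits would give 0.60/0.825 = 0.73 and 0.50/0.875 = 0.57.

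**Step 3, completers-only denominator.**

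- Drop-out independent of events: the expected proportion stays at 10%.
- Patients with an event drop out at 50% instead of 25% (assumed): 0.10 × 0.50 / (0.10 × 0.50 + 0.90 × 0.75) = 0.05/0.725 = 6.9%.

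**Step 4, does person-time recover the truth?**

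- With D = 0.25, expected time per patient is 0.325/0.3930 = 0.827 years. The rate is 0.0871/0.827 = 0.1054 per year, and 1 − exp(−0.1054) = 10%.
- With D = 0.40, 0.0787/0.7465 again gives 0.1054. The estimate is right in both groups when drop-out is independent of events.
- If half of the events lead to loss before they are recorded, the observed hazard is halved. The rate-based risk is then 1 − 0.90^0.5 = 5.1%, and the enrolled proportion is 0.0871/2 = 4.4%. Censoring does not repair event-related loss.

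**The case against.** The strongest reply is that the quoted sentence is a general rule for all categorical variables, and that denominators and the handling of losses are commonly left to a fuller document. That stands in part: applying the rule to events is an inference. It is the natural one, because the section does name its tests and regression families and none of them uses time at risk.

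Three stronger readings are tempting, and the documents do not support them:

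- **That the plan counts unobserved time as event-free.** It fixes no denominator. This follows only if all enrolled patients are used.
- **That any denominator understates incidence.** A completers-only proportion is unbiased if drop-out is independent of events. The 6.9% rests on an assumed link.
- **That most drop-out comes from the territorial group, so the bias is unequal.** The article says this group in particular, also cites the rural area, and applies 25% to all groups. Every group-specific rate used here is an assumption.

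The practical effect is also limited. At a 10% risk, 60 patients give about 6 events (exact 95% CI 3.8% to 20.5%). The shift to 8.7% is under one event per group (60 × 0.013 = 0.8). With no true difference, the chi-square rejection rate in the constant-hazard scenarios, at assumed risks of 10% and 20%, is about 4% to 9%, so the harm lies in the estimates more than in false positives. The article calls its analysis descriptive and its tests exploratory, and the primary outcome is WMH volume change.

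Finally, Table 2 lists medical history at every visit but shows no field for event dates. The article also does not say whether ischemic events include lesions found only on MRI, which is done at 0, 6 and 12 months. Exact-time methods do not fit such lesions directly.

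**Conclusion.** The point holds in limited form: the methods stated for yes/no outcomes do not fit a 12-month incidence when 25% drop-out is expected. With all enrolled patients as denominator, the understatement is about 13% relative, assuming even and independent drop-out. The group contrast is distorted only if drop-out differs by group, with a ratio of about 0.8 to 0.9 under the assumed splits (0.77 to 0.89 in the table). These sizes are illustrations and cannot be computed from the article alone.

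The outcome is secondary and exploratory, so this is a worthwhile low-cost improvement and not a threat to the study's main result.

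**What to change.** Add to Methods of analyses:

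- For clinically detected cerebrovascular events and myocardial infarction, keep the raw counts. Beside them, report events per person-year and 12-month cumulative incidence by group with 95% CI, counted from enrolment and censored at the last event ascertainment, with death as a competing event (Aalen-Johansen estimator).
- State that this assumes drop-out independent of events. Give a simple sensitivity analysis for event-related drop-out, for example assuming a higher event risk in drop-outs after their last contact, varied by group.
- Analyse new lesions seen only on MRI separately, among patients with a follow-up MRI, because their timing is known only to the interval between scans.

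Formal group comparisons with a Gray test or Cox model are optional, given the few events likely.

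**Cost:** slightly more analysis, and recording of event and last-contact dates. Only nine patients were enrolled at the count given under Recruitment, so adding these fields early is feasible. Intervals will be wide with few events.

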### Primary outcome

The primary outcome is the change in WMH volume based on brain MRI measurements.

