To account for scanner differences between acquisitions, WMH segmentation will be performed using a FLAIR-only automated in-house pipeline based on the half-Gaussian mixture model described by Igwe et al. [25], which models log-transformed above-mode FLAIR intensities as a two-component mixture: a half-Gaussian for normal-appearing white matter and a full Gaussian for WMH, with all five parameters estimated via expectation-maximization. The original method was validated on a single scanner and timepoint; we extend it to longitudinal cross-scanner comparison by fitting the HGMM independently per timepoint on a shared white matter territory (intersection of both timepoints’ white matter labels), with a two-pass refinement that excludes candidate WMH from the fit pool to tighten the normal-appearing white matter model. Longitudinal change is estimated through paired voxel-wise contrast at the TP1 lesion boundary, corrected for scanner offset (estimated from stable white matter) and blur mismatch, rather than by subtracting two independent segmentations. Anatomical false positives are removed through automated exclusion. Acute DWI lesions identified on the baseline MRI were registered to FLAIR space andexcluded from the WMH volume calculations at baseline, 6-month, and 12-month follow-up. This procedure ensured that longitudinal WMH measurements represented chronic white matter disease burden, independent of the baseline acute infarct.

In the pilot cohort, baseline and follow-up FLAIR were acquired on different scanners and protocols, so standard endpoint WMH segmentation could not reliably separate true lesion change from scanner-induced contrast shifts. We therefore used a scanner-aware longitudinal pipeline designed to identify the FLAIR change as biological progression rather than scanner change artifacts. Since the prospective cohort is acquired on a stable, harmonized protocol, Deep WMH and Multi-site Auto-segmentation and Registration of Subcortical White Matter Hyperintensities (MARS)-WMH-derived segmentation will additionally be evaluated, with agreement to the manual reference quantified by Dice similarity coefficient and ICC.

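### The Wilcoxon signed-rank test is named for comparing independent patient groups, and the rank-sum test is named for follow-up imaging without saying whether that comparison is within patients or between groups

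*Protocol article*

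**What the plan says.** The protocol article, under Methods of analyses, assigns tests in two places.

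- Between groups: "Group differences will be assessed according to the measurement scale and distribution using the t-test or Wilcoxon signed rank test for continuous variables".
- Imaging, in the following paragraph: "Differences in follow-up imaging with regard to the number and volume of radiological markers of CSVD will be analyzed using the Wilcoxon rank-sum test".

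Between these two sentences it plans a third analysis, for temporal change: "individual slopes will first be estimated using linear mixed-effects models with random intercepts for participants to account for within-subject correlation". The slopes are then compared between groups.

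The cohort is "stratified into three groups: (1) CSVD without acute ischemic stroke, (2) CSVD with acute lacunar ischemic stroke, and (3) CSVD with territorial ischemic stroke" (Abstract, Methods). Under Primary outcome: "The primary outcome is the change in WMH volume based on brain MRI measurements". Under Postprocessing, that change is measured within the patient: "Longitudinal change is estimated through paired voxel-wise contrast at the TP1 lesion boundary". The Sample size section reports, from 17 pilot patients, that "the mean 12-month WMH volume change was 5.30 mL (SD 6.03; standardized within-subject effect d_z ≈ 0.88", and derives within-subject and between-group sensitivities from the SD of change. On the level: "All statistical tests will be conducted using a two-sided significance level of α = 0.05".

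**The concern.** The signed-rank test ranks differences within pairs. Nothing links a patient with no acute stroke to a patient with a lacunar or territorial stroke, so no pairs exist. The test also requires equal numbers on both sides, and enrolment already stands at 5, 3 and 1 (Recruitment section). This part does not depend on how the sentence is read.

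The imaging sentence raises a second question. The rank-sum test is for independent samples. Group differences have already been dealt with in the preceding paragraph, so a sentence on differences in follow-up imaging reads most naturally as change from baseline in the same patient. For that comparison the rank-sum test treats two measurements on one person as coming from two people. The large spread of lesion volume between patients then enters the error term, although it cancels in a paired analysis. At stake would be the sensitivity to white matter hyperintensity (WMH) change that the sample-size section illustrates.

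**Working it through.** **1. The plan's own figures.** Inputs from Sample size: mean change 5.30 mL, SD of change 6.03 mL, 60 patients per group, about 45 completing. Two-sided α = 0.05 and 80% power give 1.960 + 0.842 = 2.802.

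- d_z = 5.30 / 6.03 = 0.879 (stated ≈ 0.88).
- Detectable d_z = 2.802 / √n: 0.362 at n = 60 and 0.418 at n = 45 (stated 0.36 and 0.42).
- Detectable between-group d = 2.802 × √(2/n): 0.511 at n = 60 and 0.591 at n = 45 (stated 0.51 and 0.59).

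The detectable effects reproduce. The first formula belongs to a paired test within a group and the second to an unpaired test between groups. The Wilcoxon tests named under Methods of analyses do not fit this: a paired test is named between groups, and an unpaired test is named for imaging that may be within patients.

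**2. What the rank-sum test would do if applied to baseline against follow-up.** The protocol gives no baseline WMH mean, SD or distribution, so the baseline SD (S) is an assumption here. A normal approximation shows the mechanism, with n = 45:

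- True standard error of the mean change: 6.03 / √45 = 0.899 mL.
- Standard error an unpaired test assumes, with change independent of baseline: √[(S² + S² + 6.03²) / 45].
- Power ≈ P(Z > (1.96 × assumed SE − change) / 0.899).

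For a 2.5 mL change:

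| S (mL) | Assumed SE (mL) | Approximate unpaired power |
|---|---|---|
| 5 | 1.385 | 41% |
| 10 | 2.292 | 1.3% |
| 15 | 3.288 | below 0.1% |
| 20 | 4.311 | below 0.1% |

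**3. Simulation of the two Wilcoxon tests.** n = 45, change normal with SD 6.03 mL.

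Normal baseline, 3,000 runs per setting:

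| S (mL) | 2.5 mL: signed-rank | 2.5 mL: rank-sum | 5.30 mL: signed-rank | 5.30 mL: rank-sum |
|---|---|---|---|---|
| 5 | 76% | 40% | about 100% | 99% |
| 10 | 75% | 2% | 100% | 75% |
| 15 | 76% | below 0.1% | 100% | 16% |
| 20 | 76% | 0% | 100% | 1% |

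Log-normal baseline, which is skewed. Small differences between runs are simulation error:

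| Mean/SD (mL) | 2.5 mL: rank-sum | 5.30 mL: rank-sum |
|---|---|---|
| 10/10 | about 25% | about 97% |
| 15/15 | 8% | 84% |
| 20/20 | 2% | about 57% |
| 30/25 | below 1% | about 15% |

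Signed-rank power in the log-normal settings is about 76% or more for 2.5 mL and about 100% for 5.30 mL.

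**4. Level.** With no true change, the rank-sum test on paired data rejects in at most 0.6% of runs at n = 45 under a normal baseline (0.6% at S = 5 mL, less above that). The nominal level is 5%.

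**5. The other reading.** If the imaging sentence means comparing groups on follow-up findings or on each patient's change, the samples are independent and the rank-sum test is valid. Steps 2 to 4 then do not apply, and the between-group comparison has simply been given two different Wilcoxon tests in adjacent paragraphs, of which only the rank-sum is usable.

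**The case against.** A reader might infer that the two test names have been exchanged, that the primary outcome is therefore tested with its pairing discarded, and that nearly all the illustrated sensitivity is lost. The documents do not support that, for three reasons.

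First, the imaging sentence never says baseline against follow-up. The within-patient reading is likelier, but the between-group reading is open.

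Second, pairing is kept elsewhere. Temporal change is to be analysed with mixed models that carry a participant random intercept, and WMH change is a temporal change. The imaging pipeline also measures change within the patient rather than by subtracting two separate segmentations, and comparing such change measures between groups by rank-sum loses no pairing.

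Third, the size of any loss rests on an assumed baseline spread. For the pilot effect of 5.30 mL, rank-sum power is 97% to 99% when the spread is small. Patients with Fazekas grade 1 are eligible, so a small spread cannot be excluded in some groups. The assumed shape matters too: at an SD of 10 mL and a 2.5 mL change, power is 2% under a normal baseline and about 25% under a log-normal one.

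Two further points can be made for the plan. The study is exploratory and its tests are declared hypothesis-generating, and a signed-rank test on unequal groups would fail to run, so the slip should be noticed. The missing three-group omnibus test is also no error: one stated aim is a direct comparison of lacunar with territorial stroke, and pairwise tests without multiplicity adjustment are openly declared.

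All of this limits the consequence. None of it makes the signed-rank test suitable for independent groups, or tells the analyst which comparison the imaging sentence means. An exploratory p-value still needs a test that fits the data. Nor is this a detail left to an analysis plan, since the article itself names the test.

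**Conclusion.** The point holds in two parts of different strength.

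- **Certain:** the signed-rank test is the wrong test for group differences in this design, on any reading.
- **Likely but not settled by the text:** the rank-sum test is wrong for the follow-up imaging comparison if that comparison is within patients. It would then miss its nominal level and contradict the paired sensitivity of d_z 0.36 to 0.42.

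On the within-patient reading only, with 45 completers and a 2.5 mL change, rank-sum power would range from about 40% (normal baseline, SD 5 mL) to below 1% (normal baseline with SD 15 mL or more, or log-normal with mean/SD 30/25 mL). Signed-rank power would be about 76% or more. These figures assume that change is independent of baseline, has SD 6.03 mL as in the pilot, and starts from baseline distributions the protocol does not give. They describe one named test. They do not show that the primary outcome as a whole loses its sensitivity, because the mixed models remain.

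**What to change.** Under Methods of analyses:

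- For comparisons between independent groups, including between-group comparison of WMH change, name the two-sample t-test or the Wilcoxon rank-sum test.
- For within-patient change from baseline to 6 or 12 months, name the paired t-test or the Wilcoxon signed-rank test.
- State which of these comparisons the follow-up imaging sentence covers.

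An omnibus test across the three groups may be added but is optional.

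The cost is the wording of two sentences. No data collection, sample size or patient procedure changes, and only nine patients had been enrolled at the date the protocol reports.

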The objectives of the presented study include the identification of one blood biomarker or a set of biomarkers that can help identify disease progression in CSVD. A further aim is to describe differences of biomarker courses in direct comparison of patients with CSVD and acute lacunar ischemia with patients with territorial ischemia in a prospective, consecutive and multi-modal trial.

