### Eligibility criteria

Patients are eligible as participants if (a) their age is ≥ 18 years and if (b) brain MRI provides evidence of CSVD, defined as WMH (Fazekas grade 1–3). Patients with Fazekas grade 1 will be included as well to cover all different stages of CSVD and because even a mild lesion load has been linked to neurocognitive impairment [21]. In case of uncertainty about the aetiology of WMH, diagnostics to rule out inflammatory diseases or genetic small vessel diseases are planned. Furthermore, (c) patients must be assigned to one of the following groups based on MRI findings: Group 1: CSVD without evidence of an acute ischemic stroke, Group 2: CSVD with acute lacunar ischemic stroke, defined as singular diffusion-weighted imaging (DWI)-hyperintense, apparent diffusion coefficient (ADC)-hypointense lesion on brain MRI with a diameter of maximum of 2.5 cm, or group 3: CSVD with acute territorial ischemic stroke pattern on MRI. All patients must be (d) able to provide written informed consent and (e) have sufficient German language skills to understand study procedures and assessments. The requirement for sufficient German language skills is necessary to ensure valid neuropsychological assessments. However, this criterion may introduce selection bias and may limit the generalizability of the study findings.

Inclusion criteria are as follows:

Age ≥ 18 years.Evidence of CSVD on brain MRI, defined as the presence of WMH (Fazekas grade 1–3).Assignment to one of the defined study groups based on MRI findings.Ability to provide written informed consent.Sufficient German language skills.

Exclusion criteria are as follows:

Alternative plausible causes of WMH other than CSVD.Known neurodegenerative diseases.Acute or recent traumatic brain injury.Contraindications to MRI.Pregnancy or breastfeeding.Expected life expectancy of less than one year.Inability to comply with study procedures or follow-up visits.Severe renal insufficiency with an estimated glomerular filtration rate <15 ml/min

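### For continuous variables, including the primary outcome, the plan names only two-sample or paired tests for a three-group design and does not carry the lacunar-versus-territorial comparison into the analysis

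*Protocol article*

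**What the plan says.** The Abstract states that participants are "stratified into three groups", and the Eligibility criteria repeat that "patients must be assigned to one of the following groups based on MRI findings": CSVD without acute stroke (Group 1), with acute lacunar stroke (Group 2) and with acute territorial stroke (Group 3). The primary outcome, change in WMH volume, is continuous.

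Under Methods of analyses, group differences are assessed "using the t-test or Wilcoxon signed rank test for continuous variables" "and the chi-square test or Fisher’s exact test for categorical variables". Differences in the number and volume of imaging markers at follow-up go to the Wilcoxon rank-sum test. Individual slopes from mixed models are then compared between groups by a test that is not named. Regression or mixed models follow as a further step, for group differences found notable.

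On error rates the section is open: "All statistical tests will be conducted using a two-sided significance level of α = 0.05", "No adjustment for multiple testing will be performed", and "all statistical test results will be interpreted as hypothesis-generating rather than confirmatory".

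The objectives at the end of the Introduction include the aim to "describe differences of biomarker courses in direct comparison of patients with CSVD and acute lacunar ischemia with patients with territorial ischemia". The Sample size section gives a between-group sensitivity without saying which pair of groups it refers to.

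**The concern.** The tests named for continuous variables do not fit the design. A t-test compares two means. The rank-sum test compares two independent samples. The signed rank test compares paired values and does not apply to separate groups of patients. None of them answers whether WMH change, or a biomarker, differs across the three groups.

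An analyst following the section must therefore choose pairs, and it does not say which pairs or in what order. The objectives suggest that Group 2 versus Group 3 comes first for biomarker courses, but the analysis section does not take this up. For the primary outcome no contrast is named anywhere. This matters because a notable group difference sends a variable on to regression, and the reader cannot tell which comparison, out of how many, made it notable.

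**Working it through.** **1. Which named tests can take three groups**

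| Step in Methods of analyses | Test named | Can compare three independent groups at once? |
|---|---|---|
| Continuous variables | t-test | No |
| Continuous variables | Wilcoxon signed rank | No; paired data |
| Follow-up imaging markers | Wilcoxon rank-sum | No; two samples |
| Categorical variables | Chi-square, Fisher's exact | Yes |
| Comparison of slopes | Not named | Not excluded |
| Follow-up regression, mixed models | Named by type only | Yes, if group enters as a three-level factor |

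The gap is confined to continuous variables. These include the primary outcome.

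**2. The plan's own between-group figure**

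Inputs from Sample size: 60 per group, 25% drop-out, so 60 × 0.75 = 45 completers; SD 6.03 mL; two-sided 0.05; 80% power. The formula for one pairwise comparison is d = (1.960 + 0.842) × √(2/n).

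- n = 60: 2.802 × √(2/60) = 0.511, and 0.511 × 6.03 = 3.08 mL.
- n = 45: 2.802 × √(2/45) = 0.591, and 0.591 × 6.03 = 3.56 mL.

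Both match the stated 0.51 to 0.59 and 3.1 to 3.6 mL. The planning figure is thus for a single pair of groups.

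**3. Error rate if all three pairs are tested**

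Three groups give 3 × 2 / 2 = 3 pairs. With equal groups and a 0.05 test on each pair, at least one rejection occurs when the largest pairwise |z| exceeds 1.960. In terms of the studentized range for three means this is P(Q > 1.960 × √2 = 2.772) = 12.2% in large samples. Simulating three two-sample t-tests (400,000 null studies) gives 12.1% at 60 per group and 12.3% at 45. For reference, three independent tests would give 1 − 0.95³ = 14.3%, and the Bonferroni bound is 3 × 0.05 = 15%. The true value is lower because the pairs share groups.

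This calculation assumes that all three pairs are tested, which the article does not state.

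**4. How the lead contrast should be estimated**

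One option is to take the error variance from all three groups. At 45 per group this raises the degrees of freedom from 2 × 44 = 88 to 3 × 44 = 132, which moves the critical value only from 1.987 to 1.978. It also assumes equal variances, for which the article gives no support. As an assumption, let the territorial group's SD be 1.5 to 2 times that of the others. The pooled Group 2 versus Group 3 contrast then rejects falsely in 6.8% to 8.0% of null studies, against about 5.1% for the two-sample test. Pooling gains almost nothing and can do harm.

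**The case against.** The strongest reply is that the plan is exploratory and says so. It declares no adjustment, calls every test result hypothesis-generating, and bases the sample size on feasibility. It promises no familywise rate, so none is exceeded. This stands: the 12% cannot be presented as a loss of error control. What the disclosure does not do is supply a test that fits three groups or say which contrast is read first.

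A reader might infer four stronger things that the article does not support:

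- That groups are compared by two-sample tests only. Chi-square and Fisher's exact test handle three groups, and neither the slope comparison nor the regression step rules out a three-level factor.
- That every variable is tested three times. The article does not say so; one or two chosen pairs would also fit its wording.
- That the study has no lead contrast. The objectives name lacunar versus territorial for biomarker courses. What is missing is its place in the analysis section, and any contrast for WMH change.
- That an overall test must be passed before any pair is examined, or that Bonferroni is needed. In an exploratory study these are trade-offs. Bonferroni at 0.05/3 would cut power at the stated d from 80% to about 66%.

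It could also be said that details of testing belong in a separate analysis plan. That would excuse silence, but here the article names specific tests, and for continuous variables they do not match the design.

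**Conclusion.** The point holds for continuous variables, including the primary outcome. No named test addresses whether the three groups differ, and the comparison singled out in the objectives is not carried into the analysis. If all three pairs were tested at 0.05, about 12% of null cases per continuous variable would show at least one false difference. That figure assumes equal groups and roughly normal data, and in an openly unadjusted plan it describes how to read the results without breaching any commitment. The defect is a mismatch between the named tests and the design, together with an unspecified set of contrasts.

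**What to change.** In Methods of analyses, replace the sentence on continuous variables so that:

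- group enters as a three-level factor: ANOVA or Welch ANOVA, Kruskal-Wallis where ranks are used, and a group-by-time term in the mixed model for repeated measures, with the 2-df group test reported (for group-by-time, 2 df if time is linear);
- Group 2 versus Group 3 is reported as the lead contrast, for WMH change as well as for biomarkers, estimated directly with a method that does not assume equal variances across groups (for example Welch's t-test with a confidence interval);
- the comparisons of Group 1 with Groups 2 and 3 are labelled secondary and unadjusted;
- the signed rank test is kept for paired, within-patient comparisons only.

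The overall test is reported alongside the contrasts and does not gate them. The change therefore does not lower the 12% when all three pairs are read as equals. It answers the three-group question and tells the reader which contrast comes first.

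The cost is a few lines of text and one extra overall test per variable. No patients or data are added, and the stated sensitivity for a single pairwise comparison is essentially unchanged. With nine patients enrolled by 11 June 2026 (Recruitment), the wording can be settled while follow-up is at an early stage.
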